##### Abortion Related Outcomes

Abortion related outcomes will be measured according to women’s gestational weeks at abortion, type of abortion, complications, and follow-up-exam attendance.

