### 2.9. Data Analysis

Participant characteristics, feasibility outcomes, and quantitative acceptability outcome data will be summarized with descriptive statistics, including frequency counts and percentages (categorical variables) and mean with 95% confidence intervals (CIs) or standard deviation (continuous variables). Intervention feasibility and acceptability will be assessed against the following criteria: eligibility: ≥60% of patients screened will be eligible; recruitment: ≥80% of eligible participants will agree to participate; protocol fidelity: ≥90% of patients randomized to each group will receive the allocated intervention; retention: <20% of patients will be lost at 6 weeks after abortion; and missing data: <20% of data will be missing. Between-group differences of participant characteristics, baseline data, and effectiveness outcomes will be detected using Statistical Package for the Social Sciences (SPSS)^®^ version 23 [41]. Specifically, Chi square tests will be used for categorical/dichotomous variables, and *t*-tests or Mann–Whitney U tests for continuous variables (depending on normality). To capture changes in the effect outcomes over time, a general linear regression analysis will be performed. See Table 3 for the specific analysis approaches.

For qualitative data, audiotapes of telephone interviews will be transcribed and de-identified by the primary researcher. Transcripts and notes will be analyzed using the deductive approach of content analysis [42]. First, a structured analysis matrix will be developed based on the aims of the study and the TFA of Health Care Intervention. Then the primary researcher and nurse coordinator will independently review all de-identified data, and content fit the matrix. They will work together to group similar content within the matrix boundaries as categories, and then main categories. After abstraction of each category, the primary researcher and nurse coordinator will make a joint decision on how to model and report the results. Any discrepancies along the process will be discussed with a third reviewer until an agreement is reached. To preserve the original meaning of women’s statements, the data analysis process will be conducted using Chinese. Development of the analysis matrix and reporting process will use Chinese and English to reduce potential bias and build a shared vision among the research team.

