**8.** **WHEN and HOW MUCH**	Consultation (after women made their abortion appointment, 30 min) Information booklet (during the consultation, one copy to take home) Public profile page (from the consultation, unlimited access until the closure of the project) Hotline (from the consultation, available during workhours)	Prior abortion consultation—at women’s first appointment (10–20 min); Abortion preparation education—after women made their abortion appointment (5–10 min); post-abortion education—before women are discharged (10 min); The post-abortion exam—2 weeks after abortion
**9.** **TAILORING**	Participants in the intervention group will receive the same intervention	N/A
**10.** **MODIFI-CATION**	Cannot be reported until the study is complete	N/A
**11.** **HOW WELL**	The research nurse and reception nurses involved in the trial will be trained initially. A researcher logbook will be kept recording intervention delivery of each participant. Adherence to the intervention will be assessed by participants self-reported usage info collected during follow-ups	N/A
**12.** **ACTUAL**	Cannot be reported until the study is complete	N/A

Abbreviations: Q&A: questions and answers; N/A: not applicable.

**Table 2 ijerph-19-06611-t002:** Content of the information booklet and platform.

Categories	Themes	Example Items
Abortion	Facts about abortion	General information about abortion Pregnancy calculation and ectopic pregnancy Abortion practice in Beijing
	Different types of abortion	Medical abortion and steps involved Aspiration/surgical abortion and steps involved Features of aspiration abortion and medical abortion
	Q&A	What is your legal position, e.g., gestation age limits; no need for husbands’ or partners’ permission; and Nation ID required etc. How much does abortion cost? Does abortion hurt and what is a painless induced abortion? What will you experience during an abortion? How could you know your abortion is complete? Will an abortion cause infertility? How will you feel if you have an abortion
	Aftercare and follow-up examination	Follow-up examination and why it is necessary Symptoms requiring contacting your health provider, going to local emergency room, or calling 120 for Emergency Health Aid.
Intimate Relationship	A healthy relationship	Important characteristics of a healthy relationship Rights and responsibilities in a relationship Equality in intimate relationships

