	Identify and deal with a dangerous relationship	Signals of unhealthy relationships Options for women experiencing an unhealthy/dangerous relationship Recognising Intimate Partner Violence (IPV) Options for women experiencing IPV
	About sex	Consent and your legal position Options for women who are forced to engage in a sexual activity
Available Coping Resources	Coping with abortion experience	Suggestions from experts (Chinese Health & Medical Development Foundation) Suggestions from women who have experienced an abortion
	Taking care your emotions	Talk to someone you trust: Tips on finding a reliable person to talk to (Marie Stopes China) Medication: free medication; Apps recommendation e.g., Tide Reading: e.g., Trauma and Recovery by Judith Herman _Chinese version Post-abortion counsellor
	Cope with IPV or sexual violence experience	Free social support services e.g., Beijing Women’s Federation hotline; The Maple Women’s Psychological Counselling Center hotlines etc. Self-help guides e.g., Guidelines for dealing with sexual assault (Marie Stopes China); SARSAS Suggestions from police Stories from IPV survivors

Abbreviations: ID: identification; IPV: intimate partner violence; Q&A: questions and answers; SARSAS: Self-help guide to rape and sexual abuse—Chinese version.

**Table 3 ijerph-19-06611-t003:** Data collection schedule and analysis method.

Concept (What)	Time (When)	Method (Who, Where, and How)	Measure (by What)	Method of Analysis
**Participant characteristics**	T-0	Primary researcher, at the clinic, face to face	Self-design questionnaire on sociodemographic characteristics, health history, and current gestation	Descriptive statistics X^2^ test comparing differences between groups of categorical/dichotomous variables *t*-test/Mann–Whitney U test comparing differences between groups of continuous variables

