**Effectiveness outcomes**				
Depression	T-0, -1, -2, -3	Primary researcher (T0, 3) and nurse coordinator (T-1, -2); at clinic facilities; face to face (T-0, -1, -2) and by telephone (T-3)	SMD-A	Descriptive statistics *t*-test/Mann–Whitney U test comparing baseline to T-3 *t*-test/Mann–Whitney U test comparing differences between groups at T-3 Linear regression measuring change over time
Perceived support	T-0, -1, -2, -3	As above	MOS-SSS	As above
Intimate relationship	T-0, -1, -2, -3	As above	CSI-4	As above
Coping behaviours	T-0, -2, -3	As above	CBCI	Descriptive statistics *t*-test/Mann–Whitney U test comparing baseline to T-3 of each coping style *t*-test/Mann–Whitney U test comparing differences between groups of each coping style at T-2 and T-3
Self-efficacy	T-0, -2, -3	As above	GSE-10	Descriptive statistics *t*-test/Mann–Whitney U test comparing baseline to T-3 *t*-test/Mann–Whitney U test comparing differences between groups at T-2 and T-3
Post-abortion growth	T-2, -3	As above	PTGI-SF	Descriptive statistics *t*-test/Mann–Whitney U test comparing T-2 to T-3 *t*-test/Mann–Whitney U test comparing differences between groups at T-2 and T-3
Abortion outcomes	T-3	As above	Self-design questions	Descriptive statistics Chi Square test comparing differences between groups at T-3

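### Table 3 gives chi-square as the only test for the abortion outcomes, although gestational weeks at abortion is naturally numeric and probably determined largely by gestation at T-0

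*Protocol article*

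**What the plan says.** Section 2.4.3 (Abortion Related Outcomes) lists four measures: "gestational weeks at abortion, type of abortion, complications, and follow-up-exam attendance". The first is naturally a number; the other three are categorical.

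The Abortion outcomes row of Table 3, under Effectiveness outcomes, assigns the group descriptive statistics and "Chi Square test comparing differences between groups at T-3". It names no second test and does not restrict chi-square to some of the outcomes.

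Section 2.9 gives a general rule: "Chi square tests will be used for categorical/dichotomous variables", with a t-test or Mann–Whitney test for continuous ones. It then adds "See Table 3 for the specific analysis approaches".

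Three further places bear on gestational age:

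- The Participant characteristics row of Table 3 has a T-0 questionnaire on "sociodemographic characteristics, health history, and current gestation". Section 2.8 places T-0 before randomization.
- Table 1, item 8, times the START session as "Consultation (after women made their abortion appointment, 30 min".
- The Discussion says in general terms that the analysis will be adjusted for baseline differences between the groups. It names no outcome or covariate.

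**The concern.** There are two linked problems.

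First, the general rule and the specific instruction disagree for gestational weeks. Because section 2.9 hands the specifics to Table 3, a reader who follows the document would apply chi-square to a numeric variable. That ignores the ordering of the weeks and spreads the data over many thin cells. If the analyst instead falls back on the general rule, the choice between the two is left open until the data are seen.

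Second, neither test uses gestation at T-0. The appointment is booked before the consultation, so START can act only on what remains of the wait. Most of the variation in weeks at abortion would then come from how far along women were when they presented. An unadjusted comparison listed as an effectiveness outcome would mostly reflect the chance balance of a baseline variable, and a change in waiting time would be hard to see.

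**Working it through.** **Text against table.** Table 3 spells out both kinds of test where both are meant: the Participant characteristics row names chi-square for categorical and t-test/Mann–Whitney for continuous variables. The Acceptability row limits chi-square to categorical variables. The Abortion outcomes row does neither, so it cannot easily be read as shorthand for the rule in section 2.9.

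**Inputs.** The plan gives no power figure for this row, so there is none to reproduce. Section 2.5 gives 45 women per arm recruited and 72 in total after 20% attrition, which is 36 per arm; 40 per arm lies between. The following are assumptions, because the documents give no values: SD of T-0 gestation 1.5 weeks; mean wait about 0.6 week; SD of the wait 0.5, 0.8 or 1.0 week, independent of T-0 gestation; true shift 0.4 week (about 3 days).

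**Size of a chance imbalance at T-0.** The standard error of the difference in mean T-0 gestation is 1.5 × √(2/40) = 0.335 week, so 95% of chance differences lie within ±1.96 × 0.335 = ±0.66 week. That is wider than the assumed effect of 0.4 week.

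**Unadjusted t-test.** The outcome SD is √(1.5² + wait SD²), and the standardised effect is 0.4 divided by it.

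**Adjusted for T-0 gestation.** The residual SD is the wait SD, so the standardised effect is 0.4 / wait SD.

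Power for both comes from the noncentral t distribution with noncentrality d × √(40/2), two-sided alpha 0.05. Chi-square on completed weeks was simulated.

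| Wait SD (weeks) | Share of variance from T-0 gestation | Unadjusted SD | d unadjusted | Power, t-test | d adjusted | Power, adjusted |
|---|---|---|---|---|---|---|
| 0.5 | 2.25/2.50 = 90% | 1.58 | 0.25 | 20% | 0.80 | about 93–94% |
| 0.8 | 2.25/2.89 = 78% | 1.70 | 0.24 | 18% | 0.50 | about 59–60% |
| 1.0 | 2.25/3.25 = 69% | 1.80 | 0.22 | 16% | 0.40 | about 42% |

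Chi-square on completed weeks has power of about 5–6% in these scenarios, close to the significance level itself. About half of its expected cell counts are below 5.

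**A different assumption.** With a larger shift of half an SD (T-0 SD 1.5 to 2 weeks, 36 to 45 per arm), chi-square on completed weeks has 18–28% power against 50–68% for the t-test or Mann–Whitney test. The ordering is the same, but the contrast is smaller.

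**The categorical outcomes.** For attendance of 60% against 90% (assumed), chi-square has 86% power at 36 per arm and 94% at 45. For complications the document gives no rate. At an assumed 10%, expected events are 36 × 0.10 = 3.6 or 45 × 0.10 = 4.5 per arm. A table of 4/36 against 0/36 then gives p = 0.040 by Pearson chi-square and 0.115 by Fisher's exact test. Over assumed rates of 1% to 10%, however, the true size of the nominal 5% Pearson test runs from about 0.1% to 6.0%, so it is mostly conservative.

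**The case against.** The best defence is that section 2.9 already holds the right rule for continuous variables, that three of the four outcomes suit chi-square, and that the Discussion promises adjustment for baseline differences. Gestation is compared between arms at T-0, so an imbalance would be seen. The questionnaire is not shown and might record gestation in bands. These points reduce the weight of the issue but do not remove it. Section 2.9 points to Table 3 for specifics, and the general statement on adjustment does not reach this row.

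The unadjusted test is also valid under randomization: its false-positive rate is nominal, and the loss is in precision. Further, if the wait is already booked, START may hardly move it, and 0.4 week is two-thirds of the assumed mean wait. Both remarks are fair. They bear on how much could be gained, and they equally suggest that a descriptive summary might suffice.

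A reader might go further and infer that the whole row can detect almost nothing. The documents do not support that: chi-square is suitable for type of abortion and attendance, and large attendance differences are detectable. A reader might also infer that sparse complications would lead to a false safety difference being declared. The plan announces no such declaration, no complication rate is given, and the long-run error of the test is at most about 6%. Fisher's test would change individual p-values without raising power, and providing for it is ordinary analysis-plan detail.

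**Conclusion.** The contradiction between section 2.9 and the Abortion outcomes row of Table 3 is real for gestational weeks at abortion, and the row ignores a covariate that is already collected. That chi-square is the weakest choice for this variable, and adjustment for T-0 gestation the strongest, holds in every adjusted scenario examined. The size of the gain does not rest on documented figures: adjusted power ranges from about 93% down to about 42% as the assumed SD of the wait goes from 0.5 to 1.0 week, against 16–20% unadjusted and about 5–6% for chi-square. That weeks at abortion mostly reflects T-0 gestation is an inference from the order of events. The point is minor: it affects one secondary outcome of a preliminary-efficacy objective, and neither the primary outcome nor the feasibility criteria depend on it.

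**What to change.** In the Abortion outcomes row of Table 3, separate gestational weeks at abortion from the rest. Compare it between arms with a linear model adjusted for gestation at T-0, or compare days from T-0 to the abortion, and report the difference with a 95% confidence interval. This brings the row into line with section 2.9 and with the adjustment promised in the Discussion. Keep chi-square for type of abortion, complications and follow-up attendance, with Fisher's exact test if complications prove sparse.

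The cost is one row of wording. Current gestation is already recorded at T-0 and weeks at abortion is already an outcome; the days-based alternative also needs the dates of T-0 and of the abortion.

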## Data Availability

The data involved in this study will be provided upon reasonable request to the corresponding author.
